#### Co-Development of the Core Components

The core functions of IMPACTFrail (the “what”) are informed by Singapore’s National Frailty Strategy, while the forms of delivery (the “who” and “how”) will be collaboratively developed with stakeholders in this study. Examples of specific output from this co-development stage may include: (1) IC screening questions adapted from the original WHO ICOPE screening tool (see Multimedia Appendix 2) tailored to each clinic’s clinical protocols and preferences; (2) modifications to electronic medical record systems to capture new data required by IMPACTFrail; (3) clear patient journey pathways; (4) identification of relevant clinic staff (doctors, nurses, allied health professionals, clinic coordinators, and support staff) and delegation of roles; and (5) capability building plans to prepare for the upcoming feasibility study.

#### Co-Development of Implementation Strategies

We will select, specify, and develop implementation strategies to mitigate anticipated barriers and leverage anticipated facilitators to implementation. Implementation strategies are defined as “methods or techniques used to enhance the adoption, implementation, and sustainability of a clinical program or practice” [45]. As we will conduct a smaller scale feasibility study in the next stage, each clinic will only implement a tailored set of 2-5 implementation strategies. These implementation strategies could be from the list of the 73 ERIC strategies or created inductively [32]. Each clinic could select and develop a different set of implementation strategies to align with their specific contexts.

The anticipated barriers and facilitators identified during the informal stakeholder engagement will be mapped to the CFIR determinant constructs. Subsequently, we will use the CFIR-ERIC matching tool to match CFIR-identified determinants to ERIC strategies [53,54]. The research team, polyclinic leadership, and frontline health care providers will collaboratively review the identified barriers and facilitators, the output from the CFIR-ERIC matching tool, and local contextualized considerations (eg, clinic operations, manpower) to prioritize and select implementation strategies. Strategy selection will be guided by 5 literature-informed criteria: relevance, opportunity for improvement, feasibility, level of difficulty, and validity [55]. The selected implementation strategies will be specified using Proctor framework for reporting and specifying implementation strategies across 6 domains, including actor, action target, action, temporality, dose, and implementation outcomes [45], and subsequently developed for operationalization in the feasibility study [46,56].

### Objective 2: Multisite Feasibility Study (12 Months)

#### Overall Aim

The feasibility study is defined as a small-scale assessment aimed at determining whether IMPACTFrail can be implemented at this level, evaluating its potential for scalability, and identifying how it might be adapted for broader implementation [46,56]. In other words, we seek to evaluate the readiness of implementers delivering IMPACTFrail in real-world settings at a larger scale and the preparedness of older persons to participate in the program [30,47,48]. This protocol precedes a subsequent hybrid effectiveness-implementation study that will be conducted at a larger scale with more sites and older adult participants [57,58]. The study was registered on ClinicalTrials.gov on December 22, 2024 (Identifier: NCT06753643).

#### Study Design

This will be a single-arm feasibility study conducted at five public clinics across all 3 regional health systems in Singapore. Specifically, 2 clinics were selected from each of 2 regional health systems, and 1 from the third System. Each clinic has contextualized barriers and facilitators to implementation, clinic workflows, and infrastructure. Thus, each clinic is conceptualized as a single site for feasibility testing. This study does not include a comparator arm or a pre-post design, as it does not aim to assess effectiveness. Instead, it focuses on a small-scale feasibility assessment to inform the design and implementation of a subsequent, statistically powered hybrid effectiveness-implementation. The phased approach increases the likelihood of successful real-world implementation by enabling early refinement and adaptation in practice settings.

#### Eligibility Criteria and Sample Size

Eligibility criteria include (1) registered patient of the clinic, (2) aged 60 years and older (3 of 5 clinics) or aged 65 years and older (2 of 5 clinics), (3) mildly frail, assigned by a trained health care provider as CFS score 4 or 5, and (4) able to provide informed consent independently or through a legally authorized representative. Exclusion criteria include (1) administered comprehensive geriatric assessment in the past 12 months or (2) at the time of this writing, being under the care of a geriatrician or patient of a geriatric specialist outpatient clinic.

Older adults who meet these eligibility criteria will be given information on the IMPACTFrail health care program and the research study verbally and via a hardcopy brochure by a paraprofessional care coordinator or nurse. A trained research assistant will obtain written informed consent from each older adult individually and address any queries from potential participants. Consent-taking to be recruited as a participant of the IMPACTFrail study will be conducted prior to intrinsic capacity screening. Recruitment will be conducted over approximately 9 months, continuing until each clinic reaches its target of 36 participants. All older adults will only need to go through this process once. Additionally, a subset of these older adult study participants of IMPACTFrail who participate in in-depth interviews of the qualitative study will undergo a separate informed consent process before their interviews. This informed consent-taking will be facilitated by trained researchers.

This set of consistent and unified inclusion and exclusion criteria will facilitate meaningful comparison of findings across sites and generalizability. Importantly, the broad objective is to translate the National Frailty Strategy to real-world practice. To facilitate this, the intervention will be structured around core functions that are common across all 5 participating clinics, including Clinical Frailty Scale score assignment, IC screening for mildly frail older adults, further clinical assessment, tailored referrals to clinics, specialists or community services, and monitoring and follow-up. While the form of implementation may vary across clinics, such as the precise age cut-offs for inclusion, further clinical assessment tools, and referral workflows, the underlying core functions remain consistent and intentional. This approach is aligned with the core functions and forms paradigm, recognizing that complex interventions must adapt to context while preserving their core purpose [59-61].

For the 2 of 5 clinics that will apply a slightly higher age cut-off of 65 years (instead of 60 years) for inclusion, it serves to facilitate integration of IMPACTFrail’s frailty screening with existing health programs and clinical protocols. They anticipated operational challenges and a lack of manpower to intentionally identify older adults 60-64 years old for the feasibility study.

Additionally, 2 clinics under the same regional health system have additional inclusion criteria. These criteria include (1) enrolment in Healthier SG [56], (2) absence of dementia diagnosis, and (3) active chronic disease appointments for any one of the following chronic conditions: Type 2 diabetes mellitus, chronic ischemic heart disease, congestive cardiac failure, osteoporosis, Stage 4 chronic kidney disease, and chronic obstructive pulmonary disease. These criteria are driven by contextual operational considerations within these clinics, including manpower capacity, logistics, and the need to align with ongoing preventive and management care programs for patients with chronic conditions. This more targeted approach was assessed to be more acceptable and pragmatic for small-scale feasibility testing in settings with constrained resources, while keeping the same core frailty screening, IC screening, and management functions.

Overall, this study protocol serves the purpose of disseminating knowledge on co-developing a health care intervention and implementation strategies, with built-in flexibility to accommodate system-level differences across clinics. In line with implementation research, we will subsequently assess how clinics could gradually align in eligibility criteria and protocols as IMPACTFrail scales up nationally.

No formal sample size calculation is performed, as this is a feasibility study not designed to be statistically powered for assessing effectiveness and health outcomes. There is no consensus in the literature on the required sample size for pilot and feasibility studies [62]. Recommendations of sample size vary depending on the primary objective of the study, the feasibility parameter being evaluated, or clinical scale evaluation [63-66]. Published reviews from the United Kingdom have reported median sample sizes of 30 and 36 participants per arm in feasibility studies [67,68]. In addition, clinics leads were also consulted on the practical projections of recruitment and uptake, taking into account the study timeframe and available resources. Hence, our study aims to recruit 36 older adults per clinic. This was computed based on targeting a minimum of 30 participants per site while accounting for an anticipated 20% loss to follow-up (eg, nonattendance at follow-up assessment post screening). Each clinic is conceptualized as an individual site due to contextualized barriers, workflows, and infrastructure.

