**Methods:**

For the first objective, the co-development process is guided by the United Kingdom Medical Research Council’s (MRC’s) framework for developing and evaluating complex interventions and the Framework of Actions for Intervention Development (FAID). The identification of contextual barriers and facilitators will draw on the updated Consolidated Framework for Implementation Research (CFIR) and its Outcomes Addendum. To identify individual-level behavior change barriers, we will extend this framework using the Theoretical Domains Framework (TDF). The Expert Recommendations for Implementing Change (ERIC) taxonomy guided our selection and development of implementation strategies. The collaboration involves implementation researchers, clinic leadership, frontline health care providers, and older adults. A 12-month, single-arm feasibility study will recruit 180 older adults aged 60 years and older with mild frailty (Clinical Frailty Scale score 4-5) across 5 public primary care clinics. Feasibility criteria include implementation, acceptability, practicality, and adaptability. We will narratively triangulate findings across study components to enhance the validity and credibility of the feasibility study, including (1) process evaluation using quantitative process indicators, (2) qualitative study to elicit barriers and facilitators to feasibility, sustainability and scalability, and to assess the attribution of the selected implementation strategies to implementation outcomes, (3) cost analysis, and (4) program description.

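### The target of 36 per clinic is said to keep at least 30 participants after a 20% loss, but 36 leaves 28.8 expected; the derivation is wrong as written, with minor consequence

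*Protocol article*

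**What the plan says.** Under Objective 2, the section Eligibility Criteria and Sample Size first says that no formal sample size calculation was made. It cites published median feasibility sample sizes of 30 and 36 per arm and says that clinic leads were consulted on realistic recruitment. It then gives the target, "our study aims to recruit 36 older adults per clinic", and derives it from two inputs: "This was computed based on targeting a minimum of 30 participants per site while accounting for an anticipated 20% loss to follow-up". The example of loss given there is not attending the follow-up assessment after screening.

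The same section makes 36 a recruitment figure, with enrolment "continuing until each clinic reaches its target of 36 participants". The Methods part of the Abstract gives the matching total: "will recruit 180 older adults aged 60 years and older with mild frailty (Clinical Frailty Scale score 4-5) across 5 public primary care clinics". The sample size section also treats each clinic as a site in its own right, so the minimum of 30 is a claim about each clinic.

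**The concern.** Loss to follow-up occurs among people already recruited. A 20% loss must therefore be taken from the 36, not added to the 30. Multiplying the required number by one plus the loss rate, instead of dividing by one minus it, is a common slip and always gives too small a target. Here it means that the article claims a retention property for each site that the chosen number does not have.

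What is at stake is mainly the accuracy of a stated rationale. The article presents itself as a detailed and replicable protocol, and it precedes a larger, statistically powered study. If the same allowance were carried into that study, its recruitment target would also be too low for its stated loss.

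**Working it through.** **Inputs**, all from the protocol article:
- number to be retained per site: 30 (Eligibility Criteria and Sample Size)
- anticipated loss to follow-up: 20% (same section)
- recruitment target per clinic: 36 (same section)
- clinics and total: 5 clinics, 180 participants (Abstract, Methods)

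**Reproducing the stated figure.** Retained number x (1 + loss) = 30 x 1.20 = 36. This matches the target exactly, and 5 x 36 = 180 matches the total.

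**What 36 delivers.** Recruited x (1 - loss) = 36 x 0.80 = 28.8 expected per clinic. Over five clinics, 180 x 0.80 = 144, against 5 x 30 = 150. The shortfall is 30 - 28.8 = 1.2 per clinic, or 6 overall.

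**What the stated inputs require.** Retained number / (1 - loss) = 30 / 0.80 = 37.5, rounded up to 38 per clinic, or 5 x 38 = 190 in total. Check: 38 x 0.80 = 30.4, which meets 30. The target is thus 2 recruits per clinic short, 10 overall.

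**The loss that 36 tolerates.** 36 leaves 30 if at most 6 are lost: 6 / 36 = 16.7%. It leaves 29 only if at most 7 are lost: 7 / 36 = 19.4%, which is still below the anticipated 20%.

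**Chance variation, for context.** Assume that each participant is lost independently with probability 0.20 and that clinics are independent. Neither assumption is stated in the article.

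| Recruited per clinic | Expected retained | Chance that a clinic keeps at least 30 | Chance that all five do |
|---|---|---|---|
| 36 | 28.8 | 0.40 | 0.01 |
| 38 | 30.4 | 0.66 | 0.12 |

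The two rows must be read together. Dividing by (1 - loss) secures the expected number and guarantees no minimum, so even the properly inflated target misses 30 in at least one clinic about 88% of the time (1 - 0.12).

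**The case against.** The strongest reply accepts the arithmetic and denies that it matters. The article disclaims a formal calculation and gives two other grounds for the number: one of the published medians is itself 36, and clinic leads advised on what was practical. Nothing in the article depends on 30 retained participants:
- The process indicators use all recruited participants (Study Component 1, Study Sample and Data Source).
- Uptake of follow-up assessment is itself an indicator, measured as actualized referrals over total referrals (Table 3). A referred participant who does not attend therefore still contributes to the result.
- The go criterion under Triangulation of Findings is 29 of 36 recruited and completing IC screening, a step before the loss given as the example.
- The study does not set out to assess effectiveness.

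All of this stands, and it settles the size of the point. It does not remove the point, because the same paragraph says that 36 was computed from 30 and 20%, and that computation does not give what is claimed. The other grounds support keeping 36; they do not make the sentence true.

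Three stronger readings are tempting and should be resisted. A reader might infer that the feasibility decision or an analysis is compromised; no analysis or criterion shown uses 30 retained. A reader might take the 0.40 and 0.01 for 36 as the size of the error; most of the low all-clinic figure comes from requiring five clinics to meet a floor together, since 38 per clinic reaches only 0.12. A reader might also link the go threshold of 29 to the 28.8; the threshold is 80% of 36 (28.8) rounded up, but it concerns recruitment and completed screening, so it neither supports nor contradicts the retention claim.

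**Conclusion.** Wrong as written, minor. On the article's own inputs, 36 recruits with a 20% loss leave 28.8 expected per clinic rather than at least 30. The shortfall is 1.2 expected participants per clinic, or 2 recruits per clinic against the correct inflation.

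The conclusion assumes only that the 20% applies to those recruited. That is the ordinary meaning of loss to follow-up and fits the example given; no other passage gives a different rate or base. The expected-number comparison needs no distributional assumption, whereas the probabilities above do.

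The documents do not support a call to raise recruitment to 190. The total of 180 agrees with the target of 36 and is not an error in itself.

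**What to change.** Keep 36 per clinic and 180 in total, and correct the one sentence in Eligibility Criteria and Sample Size, for example:

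> The target of 36 per clinic leaves 30 participants if loss to follow-up does not exceed 16.7%; at the anticipated 20% loss, about 29 (28.8) are expected.

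Do not replace the minimum of 30 with a minimum of 29. That would repeat the fault, since 29 are kept only if loss is at most 19.4%. It would also put a second 29 of 36 in the article beside the go threshold, which measures something else. If probabilities of keeping 30 are quoted, give those for 36 and 38 side by side, or leave both out.

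The cost is one sentence and a slightly less favourable stated figure. Recruitment, analysis and the go criterion are unchanged. The planned larger study should divide by (1 - loss) when it sets its own target.

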#### Feasibility Criteria

Table 2 describes the four feasibility assessment criteria: (1) implementation, (2) acceptability, (3) practicality, and (4) adaptability, along with the corresponding study components mapped to each criterion. The criteria are informed by the literature on feasibility studies [47]. In summary, we prioritize the need to assess the ability to carry out the new screening and integrating the core functions with existing clinical protocols (implementability), how a satisfying or attractive a new program that focuses on domains beyond the conventional chronic conditions is to health care providers and older people (acceptability), whether the resources can support such a new program (practicality), and the degree it can be improved or changed if we progress beyond the pilot (adaptability) [47]. The criteria collectively inform us on the feasibility to progress from the small-scale pilot study to a main study that will be statistically powered to evaluate effectiveness and implementation at scale.

**Table 2 table2:** Mapping of study components to feasibility assessment criteria.

Criteria	Study components
Implementation: to assess how well the program’s core components and implementation strategies are implemented as intended.	Study component 1: quantitative process indicators Study component 2: assess fidelity of implementation strategies Study component 3: qualitative study Identify deviations or adaptations of the core components Elicit barriers and facilitators perceived by implementers and older adults on implementing or receiving the program and its implementation strategies Study component 5: program description Study component 6: logic model and theory of change
Acceptability: to assess the satisfaction and adoptability of the program’s core components and implementation strategies.	Study component 3: qualitative study to identify barriers and facilitators to acceptability, adoptability, and appropriateness perceived by implementers and older adults on the program and its implementation strategies
Practicality: to assess the ability to carry out the program’s core components and implementation strategies in a sustained manner.	Study component 3: qualitative study to identify barriers and facilitators to (1) delivering the program and implementation strategies with the given resources (eg, manpower, information technology infrastructure, physical infrastructure) and (2) sustainability Study component 4: cost analysis
Adaptability: to assess the extent that barriers to implementation, acceptability, adoptability, practicality, sustainability and scalability can be mitigated. This section includes assessing if the program and implementation strategies can be adapted and refined, and if we have the ability to develop additional implementation strategies if we scale.	Study component 3: qualitative study to gain insights on (1) adaptations to the delivery of the program’s core components and implementation strategies, to facilitate implementation, acceptability, adoptability, practicality, sustainability, and scalability and (2) selecting and developing additional implementation strategies if we scale

### Study Component 1: Quantitative Process Indicators on Care Processes

#### Aim

We will collect and document a comprehensive list of quantitative process indicators to measure the processes of care (Table 3). This addresses the research question on whether the program activities are delivered as planned and informs us on the follow-through of patients for the entire patient journey.

**Table 3 table3:** Process indicators.

Process indicators			Measure	Proctor implementation outcomes
**Patient recruitment**				
		Number and proportion of older adults screened for frailty using the Clinical Frailty Scale (CFS)	Volume of older adults screened for frailty using the CFS	Reach Adoption
		Number and proportion of older adults screened as CFS 4-5	Volume of older adults with mild-to-moderate frailty (CFS 4-5)	Reach Adoption
		Number and proportion of CFS 4-5 older adults referred to IC screening	Volume of older adults directed to secondary IC screening	Reach Adoption
**Intrinsic Capacity (IC) screening for CFS 4-5**				
		Number and proportion of older adults who initiated IC screening	Receptivity to IC screening	Reach Adoption
		Time between CFS screening to initiation of IC screening (in days)	Efficiency of initiating IC screening after CFS segmentation	Reach Adoption
		Number and proportion of older adults who completed all 6 domains of IC screening	Completion of IC screening after it was initiated	Reach Adoption
		Number and proportion of older adults that completed each IC domain	Completion rates of each IC screening domain	Acceptability
		Duration between initiation of IC screening to completion of IC screening of 6 domains (in days or weeks)	Efficiency of completing all 6 domains of IC screening after initiation of IC screening. For example, IC screening of 6 domains may be staggered across two visits. This indicator measures the duration between the screening of at least 1 IC domain to the completion of all 6 IC domains	Fidelity
**Follow-up assessment**				
		Number and proportion of referrals to follow-up assessment for each IC deficit	This measures care coordination: (1) number of referrals made to services for follow-up assessment for each IC deficit and (2) proportion of referrals to each service with the denominator as the total number of referrals	Reach Adoption Penetration Fidelity
		Number and proportion of actualized referrals to follow-up assessment for each IC deficit	This measures care coordination: (1) number of actualized referrals to services for follow-up assessment for each IC deficit and (2) proportion of actualized referrals to each service with the denominator as the total number of referrals	Reach Acceptability Costs

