**Downstream care pathways**				
	Number and proportion of referrals for the management of each IC deficit		This measures care coordination: (1) number of referrals made to services for management of each IC deficit and (2) proportion of referrals to each service with the denominator as the total number of referrals	Adoption Penetration Fidelity
	Number and proportion of actualized referrals for the management of each IC deficit		This measures care coordination: (1) number of actualized referrals to services for management of each IC deficit and (2) proportion of actualized referrals to each service with the denominator as the total number of referrals	Reach Penetration Costs

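### Table 3's referral proportion is a distribution across services, so it cannot show under-referral of detected deficits, and the same denominator wording leaves the actualized proportion ambiguous

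*Protocol article*

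**What the plan says.** The aim of Study Component 1 in the Protocol article is to measure whether activities are delivered as planned. It adds that the indicator list "informs us on the follow-through of patients for the entire patient journey".

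Table 3 has four referral indicators, two under Follow-up assessment and two under Downstream care pathways. Each has a count and a proportion.

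- **Referral rows.** The counts are "number of referrals made to services for follow-up assessment for each IC deficit" and, downstream, "number of referrals made to services for management of each IC deficit". The proportion in both is "proportion of referrals to each service with the denominator as the total number of referrals". Both rows are mapped to Adoption, Penetration and Fidelity; the follow-up assessment row is also mapped to Reach.
- **Actualized rows.** The counts are "number of actualized referrals to services for follow-up assessment for each IC deficit" and, downstream, "number of actualized referrals to services for management of each IC deficit". The proportion in both is "proportion of actualized referrals to each service with the denominator as the total number of referrals".

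The nearest entry to a count of deficits is in the IC screening block: "Number and proportion of older adults that completed each IC domain". That counts who finished a domain, not who was found to have a deficit in it. In its limitations, the Discussion refers to the tracked quantities as actualization rates and concedes that capture may be incomplete.

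**The concern.** A referral indicator labelled Adoption, Penetration or Fidelity should answer this question: of the people found to have a deficit, how many were referred? The denominator for that is people with the deficit. Table 3 divides by referrals instead, so people who should have been referred and were not appear nowhere in the figure.

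The unit also changes within the table. The recruitment and IC screening rows mostly count older adults; the referral rows count referrals. One person with several deficits may generate several referrals, so the number of people reached cannot be read off either.

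Follow-up assessment and care pathways are two of the program's three core functions. These rows are the only quantitative process indicators in the article for referral and uptake. Hypothesis 2 names failure to follow through after screening as an anticipated patient-level barrier. A reader of the feasibility report would look to these rows for evidence on it.

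**Working it through.** The article gives no numerical value for these proportions, so there is no figure to reproduce. The check is algebraic, followed by an illustration with **assumed** counts.

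**Notation.** For service or deficit s: D = older adults with the deficit, R = referrals made, A = actualized referrals. T = sum of R over all services. The illustration takes one service per deficit and at most one referral per person per deficit.

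**Step 1. What the denominator can mean in the referral rows.**
- Referrals to the same service: R/R = 100% always, so this reading is empty.
- All referrals together: R/T, which adds to 100% over services.
- All referrals for the same deficit: a split among the services used for that deficit, which again adds to 100%.

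D does not enter any of these. The result for the referral rows therefore does not depend on which reading is chosen.

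**Step 2. Illustration, all-referrals reading, T = 60 + 30 + 10 = 100.**

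| Quantity | Locomotion | Cognition | Hearing |
|---|---|---|---|
| R (assumed) | 60 | 30 | 10 |
| A (assumed) | 30 | 27 | 9 |
| Table 3 referral proportion, R/T | 60% | 30% | 10% |
| Referral rate R/D if D = 60, 30, 10 | 100% | 100% | 100% |
| Referral rate R/D if D = 120, 60, 20 | 50% | 50% | 50% |
| Table 3 actualized proportion, A/T | 30% | 27% | 9% |
| Attendance, A/R | 50% | 90% | 90% |

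Doubling the number of people with deficits halves the referral rate from 100% to 50%, and no Table 3 value moves. In a simpler case, 20 people have a mobility deficit, 5 are referred, and there are no other referrals. The table's proportion is 5/5 = 100%; the referral rate is 5/20 = 25%.

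**Step 3. Can the referral rate be recovered?** It needs R (in persons) and D. D is not in Table 3, and the number completing a domain does not supply it. So it cannot be derived from the table.

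**Step 4. The actualized rows.** Under the all-referrals reading, A/T = (A/R) × (R/T), that is, attendance multiplied by the service's share of referrals. For hearing, 0.90 × 0.10 = 9%; for locomotion, 0.50 × 0.60 = 30%. The per-service figure is confounded with referral volume.

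Two facts limit this:
- The sum over services is (30 + 27 + 9)/100 = 66%, which is the correct overall actualization rate.
- Attendance follows from the two counts collected: 30/60 = 50%, 27/30 = 90%, 9/10 = 90%.

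A/T is also not a share of attended traffic. That would be A/66, giving 45.5%, 40.9% and 13.6%.

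**The case against.** The strongest reply has four parts.

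1. **The actualized rows may be sound.** Each indicator is titled by IC deficit, so the total could be the total for that deficit. With one service per deficit, the illustration then gives 30/60 = 50% and 9/10 = 90%, which are proper attendance rates. The Discussion's talk of actualization rates fits this intention. This stands as a possible reading. Against it, the identical words in the referral row would then give 100% for any deficit served by one service, and a common total is the more natural reading of repeated wording. The text is ambiguous and is not shown to be wrong.

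2. **Follow-through is measurable.** A reader might infer that Table 3 cannot measure follow-through at all, or that the actualized rows merely show each service's share of traffic. The documents do not support either. Referrals and actualized referrals are both counted for each deficit, and the denominator of the actualized proportion is referrals made. Nor do the documents plan any ranking of services, so a reversed ranking is a risk of misreading and not a planned result.

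3. **A condensed article may leave indicator detail to the full protocol or analysis plan.** This is fair for data-extraction detail, and deficits must be identified at the clinic before referrals can be classified by deficit. But the article does not leave the denominator open. It states one, and that one does not measure the constructs assigned to the row.

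4. **Little turns on it.** The indicators are descriptive, and feasibility is judged by narrative triangulation with interviews. The one numerical go criterion (at least 29 of 36 recruited and completing IC screening at each clinic) uses no referral proportion. This stands and limits the severity.

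**Conclusion.** The point holds for the referral rows under every workable reading. The stated proportion is a mix of services, it does not respond to under-referral, and the referral rate cannot be derived from Table 3 because no deficit count is listed. The possible distortion has no fixed size; in the assumed examples an unchanged table is compatible with referral rates of 100% and 50%, and a reported 100% with a rate of 25%.

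For the actualized rows the finding is narrower: the denominator is poorly fixed. If it means all referrals, the per-service figure depends on referral volume and is not that service's actualization rate. The claim that follow-through cannot be measured should not be made, since overall actualization and attendance per deficit are both available from the planned counts.

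The illustrative counts are assumptions and do not come from the documents. The severity is that of a cheap correction to descriptive indicators, with no effect on the go criterion.

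**What to change.** In Table 3:

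- Add a row for the number and proportion of older adults screening positive in each IC domain, among those who completed that domain. For the management block, add the number with a confirmed deficit in each domain.
- Define the referral proportion as older adults referred for domain k divided by older adults with a deficit in domain k: screen-positive for follow-up assessment, confirmed for management.
- Define the actualized proportion as actualized referrals divided by referrals made for the same deficit or service, and state which of the two is meant.
- Keep the split of referrals across services as a separate descriptive line, labelled as such.

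The cost is one extra count per domain at each of the two stages, requested from each of the five clinics, plus the rewording. It is best settled before the clinics extract their data, because a count that was never requested may be missing at analysis.
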